## Abstract

**Background:**

Procedural sedation is essential for optimizing upper gastrointestinal endoscopy, particularly in high-risk patients with multiple underlying diseases. Respiratory and circulatory complications present significant challenges for procedural sedation in this population. This non-inferiority randomized controlled trial aims to investigate the safety and comfort of remimazolam compared to propofol for procedural sedation during upper gastrointestinal endoscopy in high-risk patients.

**Methods:**

A total of 576 high-risk patients scheduled to undergo upper gastrointestinal endoscopy are planned to be enrolled in this study and randomly allocated to either the remimazolam or propofol group. The primary outcome measure is a composite endpoint, which includes (1) achieving a Modified Observer’s Alertness/Sedation scale (MOAA/S) score ≤ 3 before endoscope insertion, (2) successful completion of the endoscopic procedure, (3) the absence of significant respiratory instability during the endoscopy and treatment, and (4) the absence of significant circulatory instability during the examination. The noninferiority margin was 10%. Any adverse events (AEs) that occur will be reported.

**Discussion:**

This trial aims to determine whether remimazolam is non-inferior to propofol for procedural sedation during upper gastrointestinal endoscopy in high-risk patients, regarding success rate, complication incidence, patient comfort, and satisfaction.

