### Randomization and allocation concealment {16}

The randomization method employs variable block randomization with random-sized blocks. Professional statisticians not involved in data management utilize the Data Web data collection management system to generate a central random sequence, randomly allocating subjects in a 1:1 ratio and dividing them into two groups. Stratification is based on whether upper gastrointestinal endoscopic invasive treatment is planned, as this factor may influence the duration of the procedure and potentially affect the sedation success rate. Random numbers are placed in coded, opaque envelopes and entrusted to personnel not involved in anesthesia or data collection for management.

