### Sample-size calculation {14}

The study plans to enroll 576 patients. The basis for sample size calculation is as follows: According to the literature report [7], patients undergoing upper gastrointestinal endoscopy and treatment with propofol sedation had a completion rate without sedation-related complications of 79%. Using a two-sample *z*-test for proportions to assess the primary outcome measure, the estimated non-inferiority margin is an absolute difference of 10% for the primary outcome measure. Setting a non-inferiority difference value of 0.1, a power (1-β) of 0.8, and a one-sided α of 0.025, a total sample size of 522 cases is required for the calculation. Accounting for an anticipated loss to follow-up rate of 10%, the total sample size is 576 cases (288 participants per group).

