### Statistical analysis

#### General principles{20a}

Continuous variables will be represented as means (standard deviations) or medians (minimum, maximum, or interquartile range), with the Shapiro-Wilk test applied to evaluate the normality of continuous variable distributions. Categorical variables will be expressed as frequencies (percentages).

All statistical analyses will involve two-sided tests, considering a *p*-value less than 0.05 to be statistically significant.

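### The abstract's non-inferiority aim extends to complications, comfort and satisfaction, but only the primary composite has a margin

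*Protocol article*

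**What the plan says.** In the protocol article, the Discussion paragraph of the abstract gives the aim: "This trial aims to determine whether remimazolam is non-inferior to propofol for procedural sedation" in high-risk patients having upper gastrointestinal endoscopy, "regarding success rate, complication incidence, patient comfort, and satisfaction". That is one type of claim applied to four domains.

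The statistical basis for a non-inferiority claim appears in Sample-size calculation {14}. There, "the estimated non-inferiority margin is an absolute difference of 10% for the primary outcome measure", and the size follows from "a power (1-β) of 0.8, and a one-sided α of 0.025, a total sample size of 522 cases is required". The Methods paragraph of the abstract repeats the 10% margin directly after defining the composite. No other margin appears anywhere in the article.

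The Primary outcome section defines success by four criteria: adequate sedation before insertion, no interruption for inadequate sedation, no low oxygen saturation during the examination, and no blood pressure or heart rate excursion during the examination.

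The Secondary outcomes section lists operator and patient satisfaction, recall, injection pain, cough and airway intervention. It also lists the individual pressure, heart rate and saturation events, both in the procedure and in the recovery room.

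For these, Efficacy evaluation {20a} names chi-square or t-tests, odds ratios with 95% confidence intervals, and Cox regression for times. General principles {20a} adds: "All statistical analyses will involve two-sided tests", with p below 0.05 as the threshold for significance.

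**The concern.** A non-inferiority claim needs a margin fixed in advance and a confidence interval compared with it. The abstract makes that claim for four domains, and the article provides the means for one. For the other three it specifies tests of a different hypothesis, namely that the arms do not differ. Such a test can show that one drug is worse or better. It cannot show that one drug is not unacceptably worse, because failing to reject equality may simply reflect limited precision.

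At stake is what the trial may conclude about individual complications, comfort and satisfaction. A reader of the abstract would expect a non-inferiority answer on each, and the stated design can give one only for the composite.

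**Working it through.** **1. Which outcome the design was sized for.** Inputs from Sample-size calculation {14}: propofol success rate 79%, margin 0.10, one-sided alpha 0.025, power 0.80. Allocation is 1:1 (Randomization and allocation concealment {16}). An equal success rate under remimazolam is assumed, since the article does not state one.

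n per arm = (1.960 + 0.842)² × 2 × 0.79 × 0.21 / 0.10² = 7.85 × 0.3318 / 0.01 ≈ 260.4, rounded up to 261, or 522 in total. This matches the article exactly, so margin, alpha, power and sample size all describe the composite and nothing else. After the allowance for loss the article plans 576, or 288 per arm.

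**2. Each domain in the abstract against what the article provides.**

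| Domain | Where it is measured | Margin | Stated analysis |
|---|---|---|---|
| Success rate | Primary composite | 10 points | Chi-square test; risk difference from a generalized linear model |
| Complications: saturation, pressure and heart rate events during the examination | Jointly in the composite; individually as secondary outcomes | Joint only | Individually: difference test, odds ratio with 95% CI |
| Complications: airway intervention, cough, all recovery-room events | Secondary only | None | Difference test, odds ratio with 95% CI |
| Comfort (no outcome bears this name; injection pain and recall are closest) | Secondary only | None | Difference test, odds ratio with 95% CI |
| Satisfaction (operator and patient, 0–10) | Secondary only | None | Difference test |

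Times, such as time to adequate sedation, are analysed by Cox regression, also without a margin.

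**3. What a non-significant complication comparison would leave open.** The article gives no rates for individual complications, so rates p of 5%, 10% and 20% in both arms are assumed. The 95% half-width for a difference with 288 per arm is 1.96 × √(2p(1−p)/288).

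- p = 5%: 1.96 × √(0.095/288) = 3.6 points
- p = 10%: 1.96 × √(0.18/288) = 4.9 points
- p = 20%: 1.96 × √(0.32/288) = 6.5 points

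With 261 per arm these become 3.7, 5.1 and 6.9 points. They are the upper limits when the observed difference is zero. A difference just short of significance would have an upper limit of nearly twice as much.

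**4. Whether margins could simply be added.** The approximate power to show non-inferiority on one complication with 288 per arm is Φ(m / √(2p(1−p)/288) − 1.96). Both the rate p and the margin m are assumed.

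| Assumed rate | m = 3 points | m = 5 points | m = 10 points |
|---|---|---|---|
| 5% | 38% | 79% | >99% |
| 10% | 22% | 52% | 98% |
| 20% | 15% | 32% | 85% |

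Only the 10-point margin gives at least 80% power at all three rates. At a 5% rate that margin would accept up to 15%, a tripling. The sample size therefore does not generally support separate claims at tighter margins.

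**The case against.** The strongest reply is that this is one sentence in an abstract. Objectives {7} does not use non-inferiority wording for the four domains, the main Discussion speaks of comparing effect and safety, and the article already labels comfort, satisfaction and individual complications as secondary. That limits the point to a mismatch of claim and design. It does not remove it, because the abstract is where the article says what non-inferiority will be judged on.

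A second reply is that the primary test is largely a safety test, since the composite includes saturation, pressure and heart rate events. This stands in part. The 10-point margin does cover those events, but jointly, together with the sedation criteria, and only during the examination. A composite can meet its margin while one component is worse, and the abstract names complication incidence separately from success rate.

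A third reply is that 95% confidence intervals are already planned. That is true, and they would allow a non-inferiority judgement if margins had been fixed. None has been.

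Two stronger readings are tempting, and the article does not support either:

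- **That non-significance will be reported as non-inferiority.** No section gives such a rule. The article leaves the step from secondary test to conclusion unstated.
- **That the many secondary outcomes create a multiplicity fault.** Nineteen items are listed (7 + 5 + 7), but some are descriptive, such as additional doses, and some overlap, such as the two cough outcomes. There is one primary endpoint. A rule for the secondary tests is commonly left to an analysis plan, which is not shown here, so its absence from the article is no fault.

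**Conclusion.** The point holds in a limited form. The abstract states a non-inferiority aim for four domains, and the stated design supports it only for the primary composite. It cannot support non-inferiority on comfort, satisfaction, any individual complication, or any event in the recovery room.

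The mismatch lies between statements in the article itself: the aim in the abstract, the single margin in the sample-size section, and the difference tests in the statistical section. It does not depend on what an unseen analysis plan may add. The half-widths and power figures do depend on assumed complication rates (and, for power, assumed margins) and serve only as illustration; the conclusion would stand without them. The primary analysis, sample size and conduct of the trial are not affected. What changes is which conclusions the trial may draw.

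**What to change.** In the Discussion paragraph of the abstract, restrict the non-inferiority aim to the primary composite. State there that individual complications, comfort and satisfaction are secondary outcomes, reported as effect estimates with 95% confidence intervals, and that no non-inferiority conclusion will be drawn from a non-significant difference.

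The cost is wording. Odds ratios and hazard ratios with 95% confidence intervals are already planned. For satisfaction scores, the mean difference with its interval would accompany the t-test. The sponsor gives up a non-inferiority claim on three domains that the design cannot support.

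Adding margins for further outcomes would be a larger step. Each would need its own justification, the sample size may not suffice, and Trial status {3} reports that enrolment began in December 2022. The wording change avoids all of that.

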**Trial registration {2a and 2b}:**

Chinese Clinical Trial Registry ClinicalTrials.gov ChiCTR2200066527. Registered on 7 December 2022.

**Supplementary Information:**

The online version contains supplementary material available at 10.1186/s13063-024-07934-z.

## Background {6a and 6b}

Gastrointestinal endoscopy is widely used for the diagnosis and treatment of digestive diseases. Midazolam and propofol are commonly utilized for procedural sedation during upper gastrointestinal endoscopy procedures [1]. Although both propofol and midazolam have demonstrated efficacy, they present specific limitations. Propofol provides desirable sedation depth and a short half-life (t1/2), enabling rapid patient recovery. However, it may cause respiratory depression, hypoxemia, and hypotension, necessitating continuous vital sign monitoring, including respiration. Midazolam, widely used, allows for easier sedation level titration compared to propofol, requiring less intensive monitoring. Its drawback is a half-life of 1–3 h [2, 3]. Remimazolam, a novel sedative and ester-based benzodiazepine, is rapidly hydrolyzed by liver esterase into its inactive carboxylic acid metabolite. With a shorter half-life than midazolam, remimazolam exhibits improved safety, facilitating swift awakening and early cognitive function restoration [4]. Phase III clinical trials of remimazolam for upper gastrointestinal endoscopy have demonstrated sedative effects and safety profiles in ASA grade (Appendix 1) I–II patients that are not inferior to propofol, with the sedative regimen outperforming propofol in certain aspects [5]. Procedural sedation safety and efficacy are primarily influenced by the patient’s physical condition. As ASA levels rise, the risk of adverse events during endoscopy increases [6]. Considering the requirements of upper gastrointestinal endoscopy, a safe and comfortable diagnostic and treatment experience during upper gastrointestinal endoscopy for these patients is important.

### Objectives {7}

This study aims to investigate high-risk patients (ASA levels III and IV) to ascertain if remimazolam can ensure a safe and comfortable diagnostic and treatment experience during upper gastrointestinal endoscopy for these patients. Additionally, this study seeks to evaluate whether remimazolam can provide optimal examination conditions for endoscopic practitioners, thereby laying a solid foundation for the widespread implementation of remimazolam in procedural sedation.

## Methods/design

### Trial design {8}

We have developed a single-center, randomized, parallel group controlled, non-inferiority trial to compare the sedative effects of remimazolam and propofol in high-risk populations undergoing upper gastrointestinal endoscopy. A total of 576 high-risk patients scheduled for upper gastrointestinal endoscopy will be enrolled and randomly allocated to either the remimazolam group or the propofol group using a block randomization method (Fig. 1). This study adheres to the principles of Good Clinical Practice for Drug Trials, in accordance with the Declaration of Helsinki. The SPIRIT checklist is provided in Additional file 1.

**Fig. 1 Fig1:**
[figure not shown]
Trial Flow

### Study setting {9}

The study will be conducted in the Second People’s Hospital of Futian District, Shenzhen, China.

#### Inclusion criteria {10}

Participants will be enrolled with the following criteria in this study: (1) age ≥ 18 years old, (2) patients scheduled to undergo upper gastrointestinal endoscopy or treatment under sedation, (3) the American Society of Anesthesiologists (ASA) classification of grade III or grade IV, and (4) patients who provide informed consent to participate in the study.

#### Exclusion criteria

Subjects will be excluded if they meet one of the following criteria: (1) Patients who decline sedation and anesthesia; (2) history of drug abuse and/or alcoholism within the past 2 years; (3) patients who have taken monoamine oxidase inhibitors or cytochrome P450 inhibitors within the last month; (4) patients with known allergies to benzodiazepines, opioids, propofol, or lidocaine, or contraindications for receiving the aforementioned drugs; (5) participation in other clinical drug trials within 3 months prior to the start of the study; (6) pregnant or lactating women.

#### Withdrawal criteria

For patients who do not meet the criteria, detailed reasons will be documented, and a case report form (CRF) will be retained for reference. The outcomes of these cases will be excluded from subsequent analyses of treatment effectiveness: (1) Loss of subject follow-up, (2) subject refusal to continue follow-up, (3) subject or their legally authorized representative requests withdrawal from the study, (4) investigator determines that the subject is unsuitable for continued study participation, (5) inability to implement trial interventions, and (6) test data not recorded.

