### Criteria for discontinuation or modification of allocated interventions{11b}

We do not plan to intentionally alter the specified interventions. However, it should be emphasized that participation in all the interventions detailed in the program is at the discretion of the individual participants. They have the freedom to choose whether to engage in or omit any of the intervention measures. Thus, if participants perceive any aspect of the intervention as less beneficial, they may opt out of that component.

The attending anesthesiologist has the authority to discontinue a participant’s involvement in the trial at any point for medical reasons. This responsibility, including the assessment of factors such as adverse reactions, lies solely with the attending anesthesiologist. Furthermore, participants have the right to withdraw from the study whenever they wish by revoking their consent.

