### Strategies for enhancing participant retention and ensuring comprehensive follow-up {18b}

There is a follow-up period, and it consists of a postoperative follow-up scheduled for one day. Participants will be assessed during this follow-up to monitor their progress and address any immediate concerns.

To promote participant retention and ensure complete follow-up, we have implemented comprehensive strategies. Typically, comprehensive follow-up is ensured by adhering to the recommendations of the anesthesiologist. These include regular communication with participants by telephone. Moreover, a meticulous effort is made to capture as many planned outcomes as possible for all participants, including those who discontinue their involvement in the study.

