#### Efficacy evaluation{20a}

Primary endpoint evaluation: In the intention-to-treat (ITT) analysis population, a chi-square test will be used to compare the success rates of patients completing endoscopic examination and treatment between the two groups. Simultaneously, a generalized linear model will be employed to calculate the unadjusted and adjusted absolute risk differences (ARD). Adjusted variables will encompass stratification indicators (invasive procedures during upper gastrointestinal endoscopy and treatment), BMI, age, concurrent respiratory diseases, concurrent cardiovascular and cerebrovascular diseases, liver and kidney function abnormalities, and operator experience. Secondary effect sizes will be presented as odds ratios (OR) with a 95% confidence interval.

Evaluation of secondary endpoints: For the intention to treat (ITT, includes all participants who were randomly assigned, regardless of whether they completed the entire study or fully adhered to the study protocol) population, chi-square test or *t*-test will be employed for comparative analysis based on variable nature (e.g., categorical variables like low oxygen saturation, hypotension, tachycardia, intraoperative awareness, recovery delay, or continuous variables such as MOAA/S, NIBP, HR, and SpO_2_). Results will be reported as odds ratios (OR) and 95% confidence intervals using a generalized linear model. Time event variables (e.g., time to achieve a MOAA/S score of ≤ 3 points after a single dose) will be analyzed using Cox regression to describe and compare the two groups, generate Kaplan-Meier curves, express results as hazard ratios (HR), and report a 95% confidence interval.

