#### Sensitivity analysis {20c}

Broaden the primary outcome measure’s success criteria to fulfill the following two conditions: (1) MOAA/S ≤ 3 points before endoscope insertion into the oral cavity and (2) no interruption due to sedation during upper gastrointestinal endoscopy and treatment. Reassess the difference in success rates between the two patient groups. B. Utilize a per-protocol (PP, only includes participants who adhered to the study protocol and completed the entire study) analysis to select specific patients for effect estimation.

Analysis population and missing data: A multiple-imputation analysis will be performed to further evaluate whether the use of indicator variables for missing data introduces bias into our results.

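### The withdrawal rule drops randomised patients whom the ITT definition keeps; followed as written, it could bias the primary comparison in either direction

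*Protocol article*

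**What the plan says.** **Withdrawal criteria.** Six reasons are listed: (1) loss to follow-up, (2) refusal of further follow-up, (3) a withdrawal request by the patient or representative, (4) "investigator determines that the subject is unsuitable for continued study participation", (5) and (6) "inability to implement trial interventions, and (6) test data not recorded". For all six: "The outcomes of these cases will be excluded from subsequent analyses of treatment effectiveness".

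**Efficacy evaluation {20a}.** For the primary endpoint: "In the intention-to-treat (ITT) analysis population, a chi-square test will be used to compare the success rates". The ITT population, used for the secondary endpoints too, "includes all participants who were randomly assigned, regardless of whether they completed the entire study or fully adhered to the study protocol".

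**Participant retention {18b}.** The trial will try to "capture as many planned outcomes as possible for all participants, including those who discontinue their involvement in the study".

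**Sensitivity analysis {20c}.** A per-protocol set is defined separately; it "only includes participants who adhered to the study protocol and completed the entire study".

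**Discontinuation {11b} and Who will be blinded {17a}.** The attending anesthesiologist alone may end a participant's "involvement in the trial at any point for medical reasons", and adverse reactions are among the factors to be weighed. The interventionists know the allocation and are also the outcome assessors.

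**The concern.** A patient who is randomised and then withdraws, is judged unsuitable, or cannot be given the intervention is out under one rule and in under the other. The primary population decides the trial's conclusion, and the protocol leaves room to choose it after the results are known.

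The exclusions need not be neutral, for two reasons.

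- Reason (4) and, in practice, reason (5) depend on staff who know the allocation. The composite fails on inadequate sedation before insertion, interruption for inadequate sedation, low oxygen saturation, or blood pressure or heart rate outside the stated limits. A patient stopped for a medical reason or not successfully sedated is therefore a likely failure.
- The primary outcome is complete when the examination ends, and the only later contact is the day-1 telephone call. As worded, reasons (1) and (2) could discard a primary outcome that has already been fully observed.

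If failures leave the denominator at different rates in the two arms, the observed difference no longer estimates the true one, and the error rate of the non-inferiority claim is no longer the planned one.

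**Working it through.** **Inputs (Sample-size calculation {14}).** Propofol success 0.79; margin 0.10; one-sided α 0.025; power 0.80; 522 evaluable, 576 enrolled (288 per arm). No separate rate is given for remimazolam, so the same 0.79 is assumed when reproducing the sample size.

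**The plan's own figure.** n per arm = (1.960 + 0.842)² × 2 × 0.79 × 0.21 / 0.10² = 260.4, rounded up to 261, or 522 in total. 261 × 1.1 = 287.1, rounded up to 288 per arm, or 576. The figures reproduce and are not at issue here.

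**Setting for the check.** Put the truth exactly at the margin: propofol 0.79, remimazolam 0.69, 288 randomised per arm. If a share e of an arm is removed and all those removed are failures, then

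- the apparent success rate is p / (1 − e), and the number analysed is 288 × (1 − e);
- P(non-inferiority) = Φ[(d + 0.10)/SE − 1.96], where d is the apparent difference (remimazolam minus propofol) and SE is the unpooled standard error.

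Worked example, 5% of remimazolam and 1% of propofol removed:

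- remimazolam 0.69/0.95 = 0.7263 (n = 273.6); propofol 0.79/0.99 = 0.7980 (n = 285.1)
- d = −0.0717; SE = √(0.7263 × 0.2737/273.6 + 0.7980 × 0.2020/285.1) = 0.0359
- (−0.0717 + 0.10)/0.0359 = 0.788; Φ(0.788 − 1.960) = 12.1%

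| Failures removed (assumed) | Apparent difference | False non-inferiority rate |
|---|---|---|
| None | −10.0 points | 2.5% |
| Remimazolam 2%, propofol 0 | −8.6 | 5.8% |
| Remimazolam 5%, propofol 1% | −7.2 | 12.1% |
| Remimazolam 10%, propofol 5% | −6.5 | 17.2% |
| 2% of each arm | −10.2 | 2.2% |
| 5% of each arm | −10.5 | 1.7% |
| 10% of each arm | −11.1 | 1.1% |
| Propofol 2%, remimazolam 0 | −11.6 | 0.8% |

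Two further cases:

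- **The same fraction of failures removed in both arms.** At 10%, 25% and 50% of failures, the error rate is 3.5%, 6.0% and 18.5%. It rises because the arm with more failures loses more of them.
- **Exclusions unrelated to outcome.** At 10% of each arm, the error rate stays at 2.5%.

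The exclusion shares are assumptions. The document gives only an anticipated 10% loss to follow-up and does not tie it to outcome.

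**Effect of keeping everyone.** No change in sample size is needed. At 0.79 in both arms, power is 83.8% with 288 per arm analysed, against 80.1% with 261.

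**The case against.** The strongest reply is that the dedicated analysis section settles the matter. It names ITT for both sets of endpoints, includes non-completers explicitly, and leaves per-protocol to a sensitivity analysis. The withdrawal section opens with a loose reference to patients who do not meet the criteria, which might mean ineligible patients only. This does not remove the conflict. Loss to follow-up, unsuitability to continue and unrecorded data describe people already in the trial, and no sentence limits the exclusion to the per-protocol set or to patients not yet randomised.

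Several stronger readings are tempting, and the documents do not support them.

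- **That the rule favours remimazolam.** A reader might infer this from the non-inferiority design. The protocol's Background and Discussion attribute respiratory and circulatory depression to propofol, so medical discontinuations could equally remove more propofol failures and count against remimazolam.
- **That unblinded staff decide all the exclusions.** This fits reason (4) and, in practice, (5). Reasons (1) to (3) come from the patient, who is blinded, or the representative; (6) is a recording failure.
- **That the 10% allowance shows how many failures would go.** It is anticipated loss, with nothing said about outcome. At 79% success about 60 of 288 patients fail (0.21 × 288 = 60.5), so removing 10% of the arm as failures (28.8 patients) would take nearly half of them.
- **That a missed telephone call certainly voids the outcome, or that a medical discontinuation is certainly excluded.** Loss to follow-up is not defined, and no passage links the anesthesiologist's authority to reason (4). The wording permits both results but states neither.
- **That the per-protocol definition selects on the outcome.** It is an ordinary condensed definition. Most component failures can occur in a patient who completes everything, and its details are commonly left to the full protocol or SAP.

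**Conclusion.** The contradiction stands. The protocol states two incompatible rules for who enters the primary analysis, and this is not a detail left to a SAP, because both rules are on the page. Followed as written, the withdrawal rule could bias the primary comparison.

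The size and direction depend on who is removed. In the unequal and equal-share scenarios tabulated, the false non-inferiority rate runs from 0.8% to 17.2%, against 2.5% planned. Even 2% of the remimazolam arm, about six patients (0.02 × 288 = 5.8), takes it to 5.8% if all are failures and no propofol patient is removed. These figures assume true rates exactly at the margin, a normal approximation, and exclusion shares that the document does not give. They show what the rule could do and do not predict what it will do. The sample size is not in error.

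This should be corrected before analysis, because it concerns the primary population and the repair is only wording.

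**What to change.** Delete the exclusion sentence under Withdrawal criteria, or confine it to the per-protocol sensitivity analysis. Then state that:

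- the primary analysis includes every randomised patient in the assigned arm, subject to the choice on use of acquired data offered at withdrawal under the consent provisions {26b};
- a primary outcome observed by the end of the examination is kept, whatever happens at the day-1 call or on later withdrawal;
- a component failure recorded before discontinuation counts as a failure under the Primary outcome definition. That definition counts only interruption for inadequate sedation, so stops for other reasons should not be turned into failures by this change;
- truly missing primary outcomes are handled by the multiple imputation already planned.

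A tipping-point check, a rule that ITT and per-protocol must agree, or a fuller per-protocol definition may be worth considering for the SAP. None of them is needed to resolve the conflict.

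The cost is wording only, with no change in sample size and no new data collection. The observed success rate may be slightly lower.
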